### Statistical analysis

Our primary analysis focuses on studying treatment policy and therefore will be conducted according to the intention-to-treat principle, that is, participants will be analyzed according to their randomized intervention group whether or not they received the intervention. However, we are also interested in understanding the impact of treatment self-selection and protocol deviations on the primary and secondary outcomes. To achieve this goal, we will also analyze the trial using the "as treated" (participants will be analyzed according to the treatment they received) and "per-protocol" (the analysis will be restricted to participants who were compliant with the treatment protocol) approaches.

### Primary outcomes: self-perceived recovery

Our primary analysis will compare the time to recovery across intervention arms using the Kaplan-Meier method. We will report the median time to recovery and 95% confidence interval (CI).[45] We will use mixed-effect Cox proportional hazards model to measure the effectiveness of the physician-based education and activation intervention and of the Soft Tissue Injury Care Model relative to the PAF. [45-49] Effectiveness will be reported as the Hazard Rate Ratio (HRR) and 95% confidence interval (CI). Participant characteristics that vary between the three interventions at baseline will be included in a multivariable Cox proportional hazards model to control for their confounding effect. Covariates added to the crude Cox Model that change any of intervention regression coefficients by 10% percent or more will be retained as confounders in the adjusted model.[50] The observations of participants who drop out of the study before they report to have recovered will be censored on the date of their last completed follow-up interview. No imputation methods will be used to deal with missing outcomes.

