## Abstract

**Background:**

Whiplash injuries are an important public health problem that is associated with significant disability and high health care utilization. Recent cohort studies suggest that physician care may be the most effective treatment for patients with whiplash-associated disorders. However, these findings have not been tested in a randomized controlled trial. The purpose of this study is to determine which of physician care or two rehabilitation programs of care is most effective in improving recovery of patients with recent whiplash associated disorders.

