**Methods and Design:**

We designed a pragmatic randomized clinical trial. A total of 444 participants (148 in each of three arms) who reside in Southern Ontario, Canada will be recruited from a large insurer. We will include individuals who are 18 years of age or older and who are diagnosed with Grade I or II Whiplash-associated Disorders. Participants will be randomized to physician-based education and activation or one of two rehabilitation programs of care currently in use in Ontario. Our primary outcome, self-rated global recovery and all secondary outcomes (neck pain intensity, whiplash disability, health-related quality of life, depressive symptomatology and satisfaction with care) will be measured at baseline by a trial coordinator and at 6 weeks, 3, 6, 9 and 12 months follow-up by an interviewer who is blind to the participants' baseline characteristics and treatment allocation. We will also collect information on general health status, other injuries, comorbidities, expectation of recovery, work status, pain coping, legal representation, and co-interventions. The primary intention-to-treat analysis will compare time to recovery between the three interventions. This trial will have 90% power at an alpha of 0.05 to detect a 20% difference in the rate of perceived recovery at one year. Secondary analyses will compare the health outcomes, rate of recurrence and the rate of adverse events between intervention groups.

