Our primary objective is to determine whether education and activation by a physician is more effective than two rehabilitation programs of care ("Soft Tissue Injury Care Model" developed by AVIVA Canada and the "Pre-approved Framework Guideline for Grade I and II Whiplash Associated Disorders" developed by the Financial Services Commission of Ontario, an arm's length agency of the Ontario Ministry of Finance) in improving recovery from WAD.

Our secondary objectives will compare the effectiveness of the three interventions on reducing neck pain intensity, reducing whiplash-related disability, improving the health-related quality of life, reducing depressive symptoms, improving satisfaction with care, shorten insurance claim durations, and reducing the recurrence rate in patients with WAD.

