### Statistical Issues

#### Sample size

Our sample size was selected to detect a difference of 20% in the rate of recovery at one year using a log rank test, a power of 90% and a two-tail significance level of 0.05.[19] Based on these parameters, we need 114 participants per group. Assuming a 30% loss-to follow-up per arm we aim to enroll a total of 444 participants (148 per intervention arm).

It is common for vehicles involved in traffic collisions to have multiple passengers. Early in our trial, we observed that some participants enrolled in the study had a spouse or relative with them in the car at the time of the collision that was also eligible for the trial. To prevent contamination bias and promote treatment compliance, we decided to change the randomization unit from the individual to the motor vehicle. Consequently, all passengers from the same vehicle are randomized to the same study arm. We have observed that less than 5% of vehicles have multiple passengers. Therefore, our original sample size of 444 participants remains valid.

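### The primary Cox analysis names hazard ratios only against the PAF, so physician care versus the Soft Tissue Injury Care Model, one of the two primary comparisons, is not pre-specified for reporting

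*Protocol article*

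**What the plan says.** The last part of the Background section gives the primary objective: to "determine whether education and activation by a physician is more effective than two rehabilitation programs of care". It then names the two programs, the Soft Tissue Injury Care Model and the PAF. The Abstract words the purpose more widely, asking "which of physician care or two rehabilitation programs of care is most effective in improving recovery".

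Under Primary outcomes: self-perceived recovery, in the statistical analysis part, the protocol opens with "Our primary analysis will compare the time to recovery across intervention arms using the Kaplan-Meier method" and promises median times with confidence intervals. It then specifies a mixed-effect Cox model for the "effectiveness of the physician-based education and activation intervention and of the Soft Tissue Injury Care Model relative to the PAF". The declared measure of effectiveness is the hazard rate ratio (HRR) with its 95% confidence interval. The same section builds an adjusted model by keeping any covariate that shifts an intervention coefficient by at least 10%.

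The analysis of secondary outcomes treats claim closure by the same Kaplan-Meier and Cox approach. Its GEE and Poisson models name no reference arm.

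**The concern.** The objective calls for two comparisons, both centred on physician care. The Cox paragraph also names two, but both are centred on the PAF. Only physician versus PAF appears in both lists.

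What is at stake is pre-specification and reporting. If the plan is followed to the letter, the report gives two hazard ratios that share the PAF arm. Their ratio gives a reader the point estimate for physician versus Soft Tissue, but its interval also needs the covariance of the two coefficients, which two published intervals do not contain. If the investigators add the contrast later, it will have been chosen after the results were visible. A second, less obvious consequence lies in the covariate rule, which depends on which coefficients the model displays.

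**Working it through.** **1. Contrasts required and contrasts named**

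| Contrast | Primary objective (Background) | Abstract's wider aim | HRR named in the primary Cox analysis |
|---|---|---|---|
| Physician vs PAF | yes | yes | yes |
| Physician vs Soft Tissue | yes | yes | **no** |
| Soft Tissue vs PAF | no | yes | yes |

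Physician versus Soft Tissue is the missing entry under both statements of the aim.

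**2. The plan's own figure**

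The Sample size section gives 114 per group for a 20% difference in one-year recovery (log-rank, 90% power, two-sided 0.05). It states no comparator recovery rate, so the figure cannot be reproduced uniquely. Assuming 50% versus 70%:
- HR = ln(0.30)/ln(0.50) = 1.737.
- Events (Schoenfeld) = 4 × (1.960 + 1.282)² / (ln 1.737)² ≈ 138.
- Per arm = 138/(0.50 + 0.70) = 115.

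Over comparator rates of 10% to 75%, the same formula gives 42 to 124 per arm. The stated 114 is thus compatible with a two-arm comparison, with equal arms throughout. Nothing in it favours one pair over another.

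**3. Can the missing contrast be recovered from the planned model?**

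Write b_P and b_S for the log hazard ratios of physician care and Soft Tissue against the PAF. Then:
- physician vs Soft Tissue = b_P − b_S
- variance = Var(b_P) + Var(b_S) − 2 Cov(b_P, b_S)

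A three-arm trial was simulated with 114 per arm and assumed one-year recovery of 50% (PAF), 50% (Soft Tissue) and 70% (physician). In one data set b_P − b_S was 0.7958 (SE 0.1777). Refitting with Soft Tissue as reference gave 0.7958 (SE 0.1777), which is identical. Over 500 data sets, power was 86.6% for physician versus Soft Tissue and 88.6% for physician versus PAF. Each figure has a simulation error of about √(0.87 × 0.13/500) = 1.5 percentage points, so the two agree. With a fixed covariate set, the choice of reference arm costs nothing.

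**4. Does the reference arm matter in the adjusted model?**

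The 10% rule looks at b_P and b_S. If each moves by less than 10%, their difference can still move by up to 0.10 × (|b_P| + |b_S|). Illustration with assumed values:

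| Coefficient (log HR) | Crude | Adjusted | Change |
|---|---|---|---|
| Physician vs PAF | 0.50 | 0.46 | 0.04/0.50 = 8% |
| Soft Tissue vs PAF | 0.40 | 0.436 | 0.036/0.40 = 9% |
| Physician vs Soft Tissue | 0.10 | 0.024 | 0.076/0.10 = 76% |

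The covariate is dropped under the PAF reference. It would be kept if physician care were the reference, because physician versus Soft Tissue would then be one of the screened coefficients. The rule can therefore select a different adjusted model depending on the reference arm.

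**The case against.** The best defence is that nothing is lost. The Cox model contains all three arms, and the missing contrast follows from it with a valid interval. The section also opens with a comparison of all arms, and the Abstract says "The primary intention-to-treat analysis will compare time to recovery between the three interventions". The PAF is a natural reference, since the protocol describes its use as mandated in Ontario for these patients.

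Much of this stands. A reader might infer that physician versus Soft Tissue can never be estimated, that the trial cannot answer its primary question, or that half of the objective is lost. The documents do not support any of these: step 3 shows that the estimate and its precision are available from the planned model. A reader might also infer that Soft Tissue versus PAF has no place in the analysis. That holds only under the narrower objective in the Background, because the Abstract's aim of finding the most effective of three makes it relevant. Nor is the PAF wrong as a reference arm in itself.

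Two things do not stand. The Kaplan-Meier description promises medians and names no pairwise test, while effectiveness is to be expressed as an HRR, so it does not fill the gap. And the claim that the reference arm is immaterial fails once the 10% rule is applied (step 4). An analysis plan that is not shown does not remove the point either, because the protocol itself fixes the contrasts.

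**Conclusion.** The point holds as a mismatch between the stated objective and the stated contrasts. One of the two primary comparisons has no named HRR, interval or test, and confounding of that comparison is not screened by the covariate rule as written. Power, data and sample size are unaffected.

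The 76% figure rests on assumed coefficients that move in opposite directions. It shows what the rule can miss, not what is likely. The relative change is large because the crude contrast is small; the absolute shift of 0.076 is less than half the standard error of 0.1777 seen in the simulated data set, which itself rests on assumed recovery rates.

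Claim closure inherits the problem because it follows the primary method. A reader might extend the criticism to the GEE and Poisson models, but those name no reference arm and the secondary objectives simply compare the three interventions, so the text shows no error there.

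**What to change.** In the primary outcome analysis section:
- Name physician care versus the Soft Tissue Injury Care Model and physician care versus the PAF as the two primary contrasts, each with HRR and 95% confidence interval. Either make physician care the reference arm, or keep the PAF as reference and state the linear contrast b_P − b_S with its covariance-based interval.
- Apply any covariate-retention rule to those two contrasts.
- Report Soft Tissue versus PAF as an additional comparison.
- Use the same contrasts for claim closure. The text requires no change to the GEE or Poisson models.

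The cost is a sentence or two, settled before the outcome data are analysed. It needs no new data, participants or sample size. The crude model is unchanged apart from how its contrasts are expressed; the adjusted model may retain different covariates.

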### Secondary outcomes

To analyze the continuous secondary outcomes (neck pain intensity, whiplash disability, health-related quality of life, depressive symptomatology, satisfaction with care), we will first compute the intervention-specific mean, standard deviation and median at each follow-up interval. Second, we will build ordinary least-square (OLS) models using generalized estimating equation (GEE) to account for the autocorrelation present in the outcomes.[51] Third, we will test whether the intervention effects are constant throughout the follow-up periods.[51] Fourth, we will test whether imbalances in the distribution of the baseline covariates confound the intervention effects. Covariates added to the crude linear model that change any of intervention regression coefficients by 10% percent or more will be retained as confounders in the adjusted models.[50] The intervention effects will be reported as the mean differences and 95% for each follow-up interval.

We will analyze time to claim closure using the Kaplan-Meier method and the Cox proportional hazards model as described above. Effectiveness will be reported as the HRR and 95% CI.

To analyze the recurrence rate, we will first compute the intervention-specific incidence (95% CI) of recurrence. Second, we will use Poisson regression and GEE to account for the autocorrelation present in the report of self-perceived recovery.[51] In the Poisson model, the number of recurrences will be used as the outcome variable. Third, we will test whether imbalances in the distribution of the baseline covariates confound the intervention effects. Covariates added to the crude Poisson model that change any of intervention regression coefficients by 10% percent or more will be retained as confounders in the models.[50] We will present the intervention effects as relative risks (RR) and 95% CI.

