### Pilot study

We conducted a pilot study from February 1 – 25, 2008. The purpose of the pilot study was to test the feasibility and implementation of the trial. Specifically, we aimed to: 1) determine the referral rate from AVIVA Canada; 2) determine the participation rate; 3) test the administration of the baseline questionnaire; 4) ensure that the interventions can be delivered in a timely fashion and according to the protocol and 6) determine the 6- week follow-up rate.

The trial coordinators received 41 referrals during the pilot study for a referral rate of 1.6 calls per day. Of those, 36 were eligible and 12 consented to participate (participation rate = 33.3%). Our baseline and follow-up questionnaires were well received by participants. The six week follow-up rate was 58.3% (7/12). One participant dropped out of the study to receive care at another clinic and four participants could not be reached to complete the follow-up interview. The interventions were delivered without any difficulties.

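### For the continuous secondary outcomes, each outcome's own baseline score is not a committed covariate; a 10% change-in-estimate rule decides whether it enters

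*Protocol article*

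**What the plan says.** The protocol article, Secondary outcomes under Statistical analysis, sets out a sequence for the continuous outcomes. After descriptive summaries, "we will build ordinary least-square (OLS) models using generalized estimating equation (GEE) to account for the autocorrelation present in the outcomes". The constancy of the intervention effect over follow-up is then tested. Next, "we will test whether imbalances in the distribution of the baseline covariates confound the intervention effects", with this rule for keeping covariates: "Covariates added to the crude linear model that change any of intervention regression coefficients by 10% percent or more will be retained as confounders". For reporting, "The intervention effects will be reported as the mean differences and 95% for each follow-up interval".

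Table 2 marks a baseline measurement for the NRS, WDQ, SF-36 and CES-D. Satisfaction is marked at follow-up visits only.

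The section states no working correlation for the GEE and says nothing on missing data. The sentence "No imputation methods will be used to deal with missing outcomes" stands in the section on the primary outcome, directly after the censoring rule for time to recovery.

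The Sample size section assumes 30% loss per arm. In the pilot, 7 of 12 participants completed the six-week interview.

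**The concern.** In a randomized trial with a linear model, the crude and the baseline-adjusted analyses estimate the same mean difference. If follow-up is complete, the gap between the two estimates reflects only chance imbalance at baseline. A rule that looks at this gap therefore does not ask whether the covariate predicts the outcome, which is what determines precision. A strongly predictive baseline score can be left out because the arms happen to be well balanced on it. It also becomes easier to leave out as the treatment effect grows, because the 10% threshold is relative to the effect.

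Two things are at stake. One is precision: confidence intervals that are wider than the collected data allow, and a final model that is not known until the data are seen. The other is robustness: a model without the baseline score has less protection if participants leave the study because of their symptoms and do so differently by arm.

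**Working it through.** **Inputs.** From the Sample size section: 114 per group, 30% loss, 148 per arm, 444 in total. The enrolment figure reproduces as 114 × 1.3 = 148.2, taken as 148, and 148 × 3 = 444. The article gives no standard deviation, correlation or sample size for the continuous secondary outcomes, so there is no plan figure to reproduce for them. With 30% loss, 148 × 0.7 = 103.6, or about 104 completers per arm. The correlation r between baseline and follow-up score is my assumption, shown over a range.

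**Step 1: what omission costs.** Adjusting for the baseline score multiplies the variance of the mean difference by 1 − r². The standard error is multiplied by √(1 − r²), and n completers act like n/(1 − r²).

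| Assumed r | 1 − r² | √(1 − r²) | SE smaller by | 104 per arm acts like |
|---|---|---|---|---|
| 0.3 | 0.91 | 0.954 | about 5% | 104/0.91 = 114 |
| 0.5 | 0.75 | 0.866 | about 13% | 104/0.75 = 139 |
| 0.7 | 0.51 | 0.714 | about 29% | 104/0.51 = 204 |

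**Step 2: when the rule omits the score.** At one visit, in SD units, adjusting shifts the estimate by roughly r × (baseline difference between arms). The rule keeps the score if this shift is at least 10% of the crude estimate. With r = 0.5 and a crude estimate of 0.3 SD, the shift must reach 0.03 SD, so the baseline difference must reach 0.03/0.5 = 0.06 SD. By chance alone that difference has standard error √(2/104) = 0.139 SD. The threshold is then 0.06/0.139 = 0.43 standard errors, which is often exceeded. At an effect of 0.5 SD the required difference rises to 0.05/0.5 = 0.10 SD.

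A simulation of three arms of 104 at one visit, with two comparisons against a reference arm and r = 0.5, shows how often the score is left out. The rule omits it in about 14% of trials when both true effects are 0.3 SD and in about 31% when both are 0.5 SD. Power lost against always adjusting was about 1 percentage point.

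**Step 3: drop-out.** A large-sample simulation used 40,000 per arm in two arms, baseline plus five visits, exchangeable correlation 0.5, a true effect of −0.3 SD and 28% to 30% lost by 12 months. It gave this bias in the 12-month difference, in SD units:

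| Drop-out depends on | Independence, no baseline | Exchangeable, no baseline | Independence, with baseline | Exchangeable, with baseline |
|---|---|---|---|---|
| Nothing (completely random) | −0.002 | −0.002 | −0.001 | −0.001 |
| Baseline score, same in both arms | 0.008 | 0.007 | 0.002 | 0.002 |
| Last score, same in both arms | 0.027 | 0.004 | 0.018 | 0.005 |
| Baseline score, opposite by arm | −0.278 | −0.142 | −0.005 | −0.007 |
| Last score, opposite by arm | −0.283 | −0.061 | −0.110 | 0.006 |

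Drop-out that acts alike in both arms does little harm under any of the four models. When it acts in opposite directions, bias is appreciable without the baseline score. The score together with a correct working correlation brings it to 0.007 SD or less.

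**The case against.** GEE is a standard and valid choice for secondary outcomes, and the article may leave missing-data detail to an analysis plan that is not shown. The precision gain rests on a correlation that the documents do not give. That correlation may be low at 12 months. For neck pain, the entry requirement of an average score of at least 3 also narrows the baseline range. All of this stands, and it is why the gain is given as a range starting at 5%.

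A reader might go further and infer that the planned GEE is valid only if data are missing completely at random, that imputation is ruled out for these outcomes, and that biased mean differences should be expected. The documents do not support this:

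- The no-imputation sentence belongs to the primary outcome and is not repeated for the continuous ones.
- GEE tolerates missingness that depends on covariates in the model. With a suitable working correlation, a linear GEE is close to valid when drop-out depends on observed scores.
- The section fixes no working correlation. The reference to ordinary least squares may hint at independence, but the stated aim is to account for autocorrelation.
- The larger biases need drop-out that differs by arm. The pilot does not show this. It reports that "One participant dropped out of the study to receive care at another clinic" and that four others could not be reached, with no arm or symptom score for any of them.

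What the objection does not answer is the covariate rule. The article states that rule outright, so it is not a detail left to another document.

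**Conclusion.** The point holds as a matter of covariate specification. The own baseline score of the NRS, WDQ, SF-36 and CES-D is collected but enters only through a data-driven rule that responds to chance imbalance. In a trial where the rule omits it, the standard error that adjustment would give is about 5%, 13% or 29% smaller at an assumed r of 0.3, 0.5 or 0.7. It would be wrong to read these figures as the expected loss. The rule often keeps the score, and at r = 0.5 the average power cost was about 1 percentage point. The stronger argument is that the final model should not be settled by chance when the alternative is free.

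The drop-out argument is secondary. Leaving the baseline score out makes the GEE more open to bias if drop-out depends on scores differently by arm. That is a possible risk, not one that the documents demonstrate, and the 30% loss is a planning assumption. It does not follow that GEE must be replaced by a likelihood-based model. Satisfaction has no baseline score, so the point does not apply to it. Only secondary outcomes are affected.

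**What to change.** In Secondary outcomes, state that the models for the NRS, WDQ, SF-36 summary scores and CES-D will in all cases include the outcome's own baseline score, together with arm by visit terms, so that the mean difference and its 95% confidence interval at each visit come from one pre-specified model. Take the own baseline score out of the 10% rule. Analyse satisfaction without a baseline score.

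GEE can be kept, with a stated working correlation other than independence. A likelihood-based repeated-measures model would be an acceptable sensitivity analysis, but it is not a required replacement.

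The cost is a change of analysis wording. No new data, visits or participants are needed, and standard software fits these models.

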### Randomization to treatment groups

Participants will be randomly allocated to one of the three intervention arms after they complete the consent process and answer the baseline questionnaire. If passengers from the same motor vehicle agree to participate, they will be randomized to the same treatment arm to minimize contamination and potentially minimize cross-over between treatment arms. Therefore, our unit of randomization is the motor vehicle. Central randomization was performed by the study biostatistician using statistical package, NQuery Advisor^® ^7.0.[19] To minimize the risk of unbalanced treatment assignment related to patient heterogeneity, we used block randomization which was stratified by clinical centre. The size of the blocks was randomly determined and vary between three, six, nine and 12 participants. The biostatistician provided the trial coordinators with a series of sealed opaque envelopes sequentially numbered by clinical centre. The study biostatistician is not involved in the selection of participants.

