### Data collection and follow-up

Table 2 summarizes the data to be collected during the trial. We will follow-up participants at six weeks, and three, six, nine and 12 months post-injury. All follow-up interviews will be conducted by a research assistant either in person at the study clinic or by telephone. The study research assistant will be blind to the treatment allocation and to the baseline characteristics of participants. However, because most outcomes are self-reported by the participants, the research assistant will not be blind to their outcomes status.

**Table 2 T2:** Measures used at baseline and follow-up interviews

**Measures**	**Baseline**	**6 Weeks**	**3 Months**	**6 Months**	**9 Months**	**12 Months**
Accident information	x					

Past history of neck pain and whiplash	x					

Numerical rating scale	x	x	x	x	x	x

Health care after accident	x					

Comorbidity questionnaire	x					

Acute 36-item short-form health survey (V2)	x	x	x	x	x	x

Work status	x	x	x	x	x	x

Expectation of recovery	x	x	x	x	x	x

Whiplash disability questionnaire	x	x	x	x	x	x

Center for epidemiological studies-depression scale (CES-D)	x	x	x	x	x	x

Vanderbilt pain management inventory	x	x		x		

Health state question	x	x	x	x	x	x

Socio-demographic characteristics	x					

Whether a lawyer or paralegal is involved in the claim	x	x	x	x	x	x

Global perceived recovery question	x	x	x	x	x	x

Satisfaction with care and treatment outcome		x	x	x	x	x

Co-interventions		x	x	x	x	x

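### The secondary GEE models are stated to handle only repeated answers, although the motor vehicle was randomized; intervals will be slightly too narrow if outcomes of vehicle mates correlate positively

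*Protocol article*

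**What the plan says.** Under Randomization to treatment groups, passengers of one vehicle who agree to take part go to the same arm: "Therefore, our unit of randomization is the motor vehicle". The Sample size section explains that this replaced individual randomization early in the trial and repeats the rule: "Consequently, all passengers from the same vehicle are randomized to the same study arm". It then gives one fact about clustering, "We have observed that less than 5% of vehicles have multiple passengers", and draws one consequence from it: "Therefore, our original sample size of 444 participants remains valid".

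The analysis section on secondary outcomes states what GEE is for. For pain, disability, quality of life, depressive symptoms and satisfaction: "we will build ordinary least-square (OLS) models using generalized estimating equation (GEE) to account for the autocorrelation present in the outcomes". For recurrence: "we will use Poisson regression and GEE to account for the autocorrelation present in the report of self-perceived recovery". Each participant supplies up to five follow-up answers: "We will follow-up participants at six weeks, and three, six, nine and 12 months post-injury". The vehicle is not mentioned in that section.

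**The concern.** An analysis should respect the unit that was randomized. Vehicle mates share the collision and the arm, and the Sample size section describes them as spouses or relatives, so many will also share a household. The same section says the unit was changed to limit contamination and to support compliance, which implies that the authors expect vehicle mates to influence one another. Positive correlation in pain, disability, satisfaction and recurrence is therefore plausible.

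The change of unit was carried into the sample size argument but not into the secondary models. A sandwich variance clustered on the participant allows for the five visits of one person. It assumes no correlation between two people in the same vehicle. Because those two are always in the same arm, positive correlation between them raises the true variance of an arm comparison above the estimated one. At stake is the width of the secondary intervals, not the treatment estimates.

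**Working it through.** **The plan's own figure.** The article needs 114 per group and allows 30% for loss: 114 × 1.30 = 148.2, taken as 148, and 3 × 148 = 444. No clustering factor enters, which agrees with the statement that the number was left unchanged. The article gives no figure for the effect of clustering on the secondary outcomes, so that has to be calculated.

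**Inputs**
- Share of vehicles with several participants: 5%, the limit in the Sample size section. The article says less than this.
- Participants in each such vehicle: not given; two assumed.
- ICC between vehicle mates: not given; 0.1 to 0.5 shown, with 1 as the mathematical bound.

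**Formula.** For clusters of unequal size m, the design effect is DE = 1 + (Σm²/Σm − 1) × ICC. The true standard error is √DE times the one that ignores the vehicle. The shortfall is 1 − 1/√DE. Actual coverage of a nominal 95% interval is 2Φ(1.96/√DE) − 1.

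**Numbers in.** Per vehicle, Σm² = 0.95 × 1 + 0.05 × 4 = 1.15 and Σm = 0.95 + 0.05 × 2 = 1.05. So Σm²/Σm − 1 = 1.15/1.05 − 1 = 0.095, and DE = 1 + 0.095 × ICC. The share of participants in a shared vehicle is 0.10/1.05 = 9.5%.

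| ICC | DE | √DE | SE too small by | Coverage |
|---|---|---|---|---|
| 0.1 | 1.0095 | 1.0048 | 0.5% | 94.9% |
| 0.3 | 1.0286 | 1.0142 | 1.4% | 94.7% |
| 0.5 | 1.0476 | 1.0235 | 2.3% | 94.5% |
| 1 (bound) | 1.0952 | 1.0465 | 4.4% | 93.9% |

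**Below the 5% limit.** With pairs in 3% of vehicles the factor is (0.97 + 0.12)/1.03 − 1 = 0.058. At ICC 0.5 this gives √DE = 1.0145, a shortfall of 1.4%. With pairs in 1% of vehicles, √DE = 1.0049, a shortfall of 0.5%.

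**Check by simulation.** The setting was 148 per arm, five visits, 5% of vehicles with two participants and 10,000 runs, with robust variance clustered by participant or by vehicle.
- ICC 0.5: mean standard error 0.0955 by participant and 0.0977 by vehicle, a ratio of 1.023, which matches the formula. Type I error was 5.9% and 5.4%.
- ICC 0.3: 0.0954 and 0.0967, a ratio of 1.014. Type I error was 5.6% and 5.3%.
- ICC 0: type I error was about 5.5% with either choice. Part of the excess over 5% is therefore not due to the vehicle; the gap between the two analyses is the relevant quantity.

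**What this means for the sample size.** At 90% nominal power, the power after clustering is Φ((1.960 + 1.282)/√DE − 1.960). This gives 89.7% at ICC 0.1, 89.2% at 0.3 and 88.6% at 0.5.

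**The case against.** The strongest objection is that the GEE cluster is never named. That it is the participant is inferred from the word used for the dependence and from silence about vehicles. A journal article often leaves the cluster identifier to an analysis plan, and one that is not shown might name the vehicle. This stands as a caution. But the article does more than stay silent: twice it states which dependence GEE is there to handle, and in neither place is it the dependence that the randomization creates.

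It can also be said that the authors considered clustering and judged it negligible. They did so for the sample size, and the power figures support them: the loss is at most about 1.4 points at ICC 0.5 with pairs. A reader might infer that 444 is too few because of the vehicles; the documents do not support that. But the low share is given only as a reason to keep the number, not as a reason to leave the vehicle out of the models.

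The size objection stands in full. The figures are ceilings for pairs: the share is below 5%, and if it counts passengers rather than enrolled participants, the relevant share is lower still, since each passenger must be eligible and consent (12 of 36 eligible people consented in the pilot). If every multi-passenger vehicle supplied three participants, the factor would be (0.95 + 0.45)/1.10 − 1 = 0.273 and the shortfall 1.3% to 6.2%, but nothing in the article supports that assumption.

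A reader might also extend the point to the primary outcome, where the article says "We will use mixed-effect Cox proportional hazards model to measure the effectiveness". The random effect is not named there. It could be the vehicle, in which case the randomized unit is already respected, or the clinical centre, which stratified the randomization. The article gives no basis for calling that model wrong, and preferring a marginal hazard ratio to a conditional one is a choice of estimand, not the correction of an error. The same holds for time to claim closure, which follows the Cox approach.

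**Conclusion.** The point holds for the GEE linear models and the Poisson recurrence model. As written, they account for repeated answers and treat participants from one vehicle as independent, although the vehicle was the unit of randomization. With positive within-vehicle correlation, the secondary intervals are slightly too narrow.

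The conclusion rests on three assumptions: that the stated purpose of GEE means clustering on the participant; that the ICC is positive, with 0.1 to 0.5 as an assumed range; and that shared vehicles hold two participants each, at the 5% limit. A smaller share gives a smaller shortfall. The matter is one of consistency between design and analysis, worth correcting because correction is nearly free. It does not extend to the primary Cox analysis or to the sample size.

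**What to change.** In the analysis section on secondary outcomes, define the GEE cluster as the motor vehicle for both the linear and the Poisson models, with participants' visits nested inside it, and base the intervals on the sandwich variance. One cluster level then covers both repeated answers and vehicle mates. At the 5% limit with pairs there would be about 444/1.05 = 423 vehicles, or 141 per arm, which is ample for a sandwich variance.

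The working correlation needs a decision, because a structure defined over one person's visits does not carry over directly to a cluster holding two people. Independence is the simplest choice. Another suitable one keeps the within-participant structure, sets correlation between vehicle mates to zero in the working matrix, and leaves the sandwich, summed by vehicle, to correct the variance.

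The cost is a vehicle identifier in the analysis file, that one decision, and intervals up to about 2% wider. No change to the sample size or to the primary model is needed for this point.
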